**Fig. 2 Fig2:**
[figure not shown]
Participant timeline SARA trial

**Table 1 Tab1:** Time schedule of enrolment, interventions and assessments

	STUDY PERIOD						
	Enrolment	Allocation	Post-allocation				
**TIMEPOINT**	***-t***_***1***_	**0**	***Day 1***	***1 wk.***	***6 wk.***	***3*** ***mos.***	***6 months***
**ENROLMENT:**							
**Eligibility screen**	X						
**Informed consent**	X						
**Allocation**		X					
**INTERVENTIONS:**							
**Mastectomy with drainage**		X					
**Mastectomy without drainage**		X					
**ASSESSMENTS:**							
***Baseline characteristics***	X	X					
***Clinical assessment seroma and complications***				X	X	X	X
***Invasive interventions***			X	X	X	X	X
***SSI***				X	X	X	X
***Cosmesis***				X	X	X	X
***Additional OPD visits***				X	X	X	X
***Wound pain***				X			

### Sample size

Based on previous studies conducted with a follow-up period of 1 year we estimate that about 10% of women in each group require seroma aspirations. If the rate of women requiring aspirations in the drain free group would be 10% larger than the overall aspiration rate of 10%, we would conclude that drain free mastectomy is inferior to standard mastectomy (i.e., the non-inferiority limit is 10%). To be able to have 80% power to reject the null-hypothesis that drain free mastectomy is inferior if in reality it is not, we need to include at least 112 patients per group. To account for a potential drop-out rate of 10% we will include 125 patients per group, or 250 in total. We expect that enrolment of these patients for the study will take 18 months.

### Interim analysis

An interim analysis will be conducted after half of the patients (112) are included. The purpose of this interim analysis is to assess whether the assumptions that have been used to inform the sample size calculation were correct (i.e., the rate of aspirations and the drop-out rate). The total sample size may be adjusted as a result of the interim analysis, thereby ensuring sufficient power to reject the null-hypothesis that drain free mastectomy is inferior at the end of the study. No primary or secondary outcome measures will be tested in the interim analysis, and the results will not contribute to the conclusions of the study.

### Randomization

Patients will be randomly assigned to one of the two groups with a 1:1 allocation as per a computer generated randomization schedule. Randomization will take place on the day of surgery, 30 min prior to wound closure. Patients will be randomized using block randomization with block sizes of 4 and allocated to one of two groups: (1) mastectomy with drain or (2) mastectomy without drain. Due to visibility of the drain no blinding is possible.

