## Methods/design

### Study design

The SARA (Seroma reduction and drAin fRee mAstectomy) trial is a single center randomized controlled trial. As it is obvious whether or not a drain is used, no blinding can be performed. Patients will be allocated to one of two groups. One group will undergo mastectomy combined with flap fixation and placement of low vacuum drainage and the other group will undergo mastectomy with flap fixation without placement of low vacuum drainage. In both groups the same method for flap fixation will be applied. Flap fixation will be achieved using sutures [10].

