### Study interventions

The operative procedure will be performed by one of four experienced breast surgeons. Dissection of the breast tissue including the prepectoral fascia is performed using electrocautery. After performing the mastectomy the extent of the skin flaps will be measured in centimeters from medial to lateral and from cranial to caudal. Wound surface is assumed to be elliptical and will be calculated using the formula A = a x b x π, see Fig. 1. The skin flaps will be sutured on to the pectoral muscle using polyfilament absorbable sutures (Vicryl 3.0), placed at 4–5 cm intervals in two or three rows, depending on the extent of the skin flaps. The distance between all sutures will be 4–5 cm. The fat of the subcutis of the skin flaps will be sutured on to the pectoral muscle. This will be performed as tension free as possible minimizing the risk of dimpling in the skin. The axillary area is not approximated using sutures. The skin edges will be sutured in one layer using absorbable monofilament sutures (Moncryl 3.0 or V-loc 30 cm), depending on the surgeon’s preference. Depending on randomization, a low suction drain will be placed before wound closure (Armstrong medical).

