### Mastectomy with low vacuum drainage

In the group with closed suction drainage, one low vacuum drain will be placed in the mastectomy gutter, lateral to the pectoral muscle before flap fixation is performed. The drain is connected to a low suction drain bottle. Drain output will be recorded daily. Drain removal will be performed once daily output is below 50 mL or after a maximum of 48 h, irrespective of drain output.

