### Concealment mechanism

Participants will be randomized using ‘ResearchManager’, which is a data management program used by Zuyderland Medical Center. Allocation concealment will be ensured, as the generated randomization schedule is protected with a password. One surgeon not involved in the treatment of these patients will have access to this password.

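### One fixed, published block size of 4 in an unblinded single-centre trial makes allocation avoidably predictable (at most one third certain), and the arm is known before the flaps are sutured

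*Protocol article*

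**What the plan says.** Under Randomization, the protocol article states that "Patients will be randomly assigned to one of the two groups with a 1:1 allocation as per a computer generated randomization schedule" and that "Patients will be randomized using block randomization with block sizes of 4 and allocated to one of two groups". No second block size and no stratification factor is mentioned. On timing it says "Randomization will take place on the day of surgery, 30 min prior to wound closure". The same section and the Blinding section say that no blinding is possible because the drain can be seen.

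Concealment mechanism rests on one safeguard: "Allocation concealment will be ensured, as the generated randomization schedule is protected with a password". The password is held by one surgeon who does not treat these patients.

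Study interventions has each operation done by one of four surgeons. Ethics and dissemination places written consent before surgery is scheduled.

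On the operation itself, Study design says "In both groups the same method for flap fixation will be applied". Study interventions specifies sutures "placed at 4–5 cm intervals in two or three rows, depending on the extent of the skin flaps". For the drain arm, the section on mastectomy with low vacuum drainage says "one low vacuum drain will be placed in the mastectomy gutter, lateral to the pectoral muscle before flap fixation is performed".

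**The concern.** A password stops someone reading the list. It does not stop someone working out the end of a block from allocations that anyone in theatre or on the ward can see. With a block of 4 and two places per arm, the remainder is known once either arm has been used twice. The block size is also public. The article appeared on 7 August 2020, and the plan was to begin inclusion in January 2020 and enrol for 18 months, so publication falls inside the planned enrolment period.

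If the next arm can be foreseen, the order of cases in theatre, or whether a consented patient is randomised at all, could depend on it. If patients with large or difficult wounds were kept out when no drain was due, aspirations in the drain-free arm would fall and the comparison would lean towards non-inferiority.

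A second route needs no prediction. Randomisation comes before flap fixation, so the surgeon knows the arm while placing the sutures. By the article's own Background, flap fixation reduces seroma, so it is the co-intervention that most needs to be equal between arms. More thorough fixation in the drain-free arm would push the result in the same direction.

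**Working it through.** **Inputs.** From the protocol article: block size 4, allocation 1:1, 250 patients, one centre, four surgeons, no blinding. Assumptions: one list, because no strata are described; and, for the lower figure only, each surgeon operates on a quarter of patients.

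**The plan's own figures.** The article gives no figure for predictability. Its sample size is used here only for the total. With 10% in each arm, a margin of 10 percentage points and 80% power, 112 per arm is reproduced at one-sided 0.05 (0.025 gives 142). Then 112/0.9 = 124.4, rounded up to 125 per arm or 250 in total, as stated.

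**Fully informed observer, fixed block of 4.** There are 6 equally likely sequences of two drain and two no-drain places. An allocation is certain once one arm is used up.

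| Position in block | Chance that it is certain | Chance that the best guess is right |
|---|---|---|
| 1 | 0 | 1/2 |
| 2 | 0 | 2/3 |
| 3 | 1/3 | 1/3 × 1 + 2/3 × 1/2 = 2/3 |
| 4 | 1 | 1 |
| Sum | 4/3 | 17/6 |

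- Certain: (4/3)/4 = 33.3%. In 250 patients there are 62 full blocks plus 2 patients, so 62 × 4/3 = 82.7, about 83.
- Best guess right: (17/6)/4 = 70.8%, against 50% under simple randomisation.

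**Surgeon who knows only their own cases and the block position.** An allocation is certain to this surgeon only if both patients who used up the other arm were their own. With a quarter of cases each, that has probability 1/4 × 1/4 = 1/16. So 33.3% × 1/16 = 2.1% of allocations.

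**Randomly varying block sizes.** These figures come from simulating 300 trials of 250 patients. The observer knows the full history and the set of sizes in use, which is more than the surgeons would be told.

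| Block sizes | Certain | Best guess right |
|---|---|---|
| 4 only | 33% | 71% |
| 2, 4 | 11% | 72% |
| 4, 6 | 5% | 69% |
| 2, 4, 6 | 4% | 70% |
| 4, 6, 8 | 2% | 68% |

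**Order of events in theatre.** Randomisation is set at 30 minutes before closure for everyone. In the drain arm the drain is placed before fixation, so the arm is explicitly known before the fixation sutures go in. For the drain-free arm the same order is inferred from the common randomisation time; no section states it. The number of rows follows flap extent, but the article gives no measurement at which two becomes three.

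**The case against.** A reader might infer that one third of allocations are in fact known in advance. The documents do not support that. It requires one person to know every earlier allocation in order and where each block starts. Nothing says that the four surgeons see each other's allocations. One third is a ceiling, and 2% is the figure under the narrower assumption above.

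A reader might also infer that surgeons select whom to enrol. Consent precedes scheduling and randomisation happens during the operation. At 250 patients in 18 months, roughly 3 a week, others will usually be randomised in between. What remains is theatre order or leaving a consented patient unrandomised, and no section gives surgeons discretion to do the latter.

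Fixation is not a free choice either. The method is common to both arms, material and spacing are fixed, and rows are tied to an extent measured in centimetres after the mastectomy. Some judgement remains because no cut-off is given. This route is also independent of block size, so changing the blocks does nothing for it.

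It is tempting to add that two or three shifted events would overturn the result. That is too loose. From 11 v 11 events in 112 per arm with a Wald interval, the upper bound passes 10% only at 15 v 11 at one-sided 0.05 (10.6%; 14 v 11 gives 9.6%), which is four more events. At one-sided 0.025 it takes three (14 v 11 gives 10.9%; 13 v 11 gives 9.9%). The article does not state the confidence level. The point here does not rest on event counts.

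Finally, varying blocks hardly improve the best guess. That stands: what they remove is certainty.

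**Conclusion.** The concern holds in limited form. A single disclosed block size of 4, with visible allocations at one centre, is avoidably predictable, and the claim that a password ensures concealment is too strong. Between about 2% and 33% of allocations are certain to an observer, depending on how far surgeons share information, which the documents do not describe. Both ends assume that the block position is known and that there is a single list; stratified lists would leave the ceiling of one third within each list for someone tracking it.

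Knowledge of the arm before flap fixation is a second, separate weakness. It is explicit for the drain arm, inferred for the other, and limited by the rules on suture spacing and rows. No actual bias is shown by either route. This is an improvement worth making because it is cheap, not a flaw that invalidates the design.

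**What to change.** 1. For allocations not yet made, regenerate the list with randomly varying block sizes, for example 4, 6 and 8. Keep the sizes in a restricted document that the surgeons do not see, and reword the concealment statement so that it does not rest on the password alone.
2. Require the flap measurements and the planned number of suture rows to be entered in the data system before the allocation can be opened. Report the rows actually placed by arm. This leaves the surgical rule as it is and makes any difference between arms visible.
3. Log every consented patient who is not randomised, with the reason, unless the full protocol already provides for this.

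The cost is a new list, one or two case report form fields and, under the article's own rule on changes that affect conduct, an amendment to the ethics committee. The flaps are already measured after the mastectomy, and no extra patients are needed. The statistical downside is a slightly larger possible end imbalance: stopping inside a block of 8 can leave the arms 4 apart, against 2 for a block of 4, which is negligible in 250.

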### Concealment mechanism

Participants will be randomized using ‘ResearchManager’, which is a data management program used by Zuyderland Medical Center. Allocation concealment will be ensured, as the generated randomization schedule is protected with a password. One surgeon not involved in the treatment of these patients will have access to this password.

### Blinding

As stated above, no blinding is possible due to the visibility of the drain.

### Data collection

The baseline characteristics and demographics will be collected preoperatively after the patient has given written informed consent. In this session the first SF-12 Health Survey questionnaire will be completed by the patient, with or without guidance of a member of the study. At the planned postoperative outpatient clinic visits at 1 week, 6 weeks, 3 months and 6 months, the patients will fill in the SF-12 Health Survey and will be asked to report on the cosmesis and experienced pain. Physical examination will take place to evaluate the wound and the presence of clinically significant seroma.

### Data management

Study data is recorded using a data management program containing case report forms (CRF’s). Data will be updated on a weekly basis. When data is exported, data is anonymized and patients can only be identified by an allocated sequence number. A coordinating investigator will verify data regularly and will check for and correct missing or inconsistent data.

### Statistical analysis

Baseline characteristics of the patients will be described in detail stratified by allocation. Continuous variables will be reported as mean and standard deviation or, in case of severe skewness, as median and interquartile range. Categorical variables will be reported as count and percentage.

Missing data will be imputed to prevent a loss of statistical precision and to reduce the likelihood of biased estimates of treatment effect. To do so, we will select a proper imputation method after careful consideration of the proportion of incomplete patients and the likely reasons for incomplete data.

#### Primary study parameter(s)

The upper bound of the confidence interval of the difference in proportion of patients that received one or more seroma aspirations during the first 6 months post-operatively will be compared to the non-inferiority limit of 10%. In case the upper bound is below the non-inferiority limit, non-inferiority will be concluded. For the primary non-inferiority hypothesis, we will perform a per protocol analysis and an intention to treat analysis as sensitivity analysis.

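### The primary comparison names no covariate, although sentinel-node status and wound surface are recorded anyway; a standardised risk difference would be a cheap, small improvement

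*Protocol article*

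**What the plan says.** Under Primary study parameter(s), the decision rests on "The upper bound of the confidence interval of the difference in proportion of patients that received one or more seroma aspirations" over six months, compared with a limit of 10 percentage points. The per-protocol analysis comes first and intention to treat is the sensitivity analysis. No covariate is named. Under Statistical analysis, baseline variables are only to be described by arm.

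Two patient-level variables are at hand:

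- **SLNB.** The inclusion criteria admit mastectomy with or without it. The share of each is not given. Study interventions adds that "The axillary area is not approximated using sutures".
- **Wound surface.** Study interventions states: "After performing the mastectomy the extent of the skin flaps will be measured in centimeters from medial to lateral and from cranial to caudal". An elliptical area is then derived ("Wound surface is assumed to be elliptical and will be calculated" from the two extents), and no exception is mentioned. The article gives the result no stated role in the analysis.

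The Background describes closing dead space as a key element in preventing seroma. On timing, the Randomization section says: "Randomization will take place on the day of surgery, 30 min prior to wound closure". The article does not say whether wound surface has been recorded by then. The trial is unblinded.

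**The concern.** On the protocol's own reasoning, a larger wound bed or an opened, unfixed axilla leaves more space for fluid, so both variables could predict aspiration. If they do, a comparison that ignores them is slightly less precise than one that uses them.

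Few events decide this trial. At 10% and 112 per arm, about 0.10 × 112 = 11 aspirated patients are expected in each arm, about 22 in all. A difference of a few patients separates success from failure.

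The point weighs somewhat more because the lead analysis is per protocol. Allocation is made during an open operation and is not blinded. If patients then leave the per-protocol set for reasons linked to the wound, the arms being compared are no longer the arms that were randomised.

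**Working it through.** **1. The plan's own sample size.** Inputs from the Sample size section: 10% in both arms, limit 10 points, power 80%. The article states no alpha or confidence level.

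n = [p₁(1−p₁) + p₂(1−p₂)] × (z₁₋α + z₀.₈₀)² / 0.10², with p₁ = p₂ = 0.10, so the bracket is 0.18.

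- One-sided 5%: 0.18 × (1.645 + 0.842)² / 0.01 = 111.3, so 112. This matches. For drop-out, 112 / 0.9 = 124.4, so 125. This matches.
- One-sided 2.5%: 142. This does not match.

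One-sided 5% is therefore used below, as an inference from the 112. The figure reproduces with no gain from covariates built in.

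**2. Unadjusted power at 112.** SE = √(0.18/112) = 0.0401. Power = Φ(0.10/0.0401 − 1.645) = 80.2%.

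**3. Effect of adjustment.** If the covariates explain a share R² of the outcome variance, the variance becomes (0.18/112)(1 − R²).

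| R² | SE falls by | Power | n per arm for 80% |
|---|---|---|---|
| 0 | 0 | 80.2% | 112 |
| 1% | 0.5% | 80.6% | 111 |
| 2% | 1.0% | 80.9% | 110 |
| 5% | 2.5% | 82.0% | 106 |
| 10% | 5.1% | 83.8% | 101 |

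The documents give no prognostic strength, so R² is an assumption. A logistic model was used with a 10% overall rate, an SLNB share of 50% to 85%, odds ratios of 1.5 to 3 for SLNB and 1 to 2 per SD of wound surface. It gives R² of about 0.2% to 7% and power of 80.3% to 82.7%, a gain of about 0 to 2.5 points.

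**4. Simulation.** 6,000 trials per scenario, 112 per arm, comparing the unadjusted difference with a covariate-adjusted risk difference.

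| Odds ratio SLNB / per SD wound surface | Power unadjusted | Power adjusted |
|---|---|---|
| 1 / 1 | 80.9% | 80.5% |
| 2 / 1.5 | 80.9% | 81.3% |
| 3 / 2 | 79.4% | 80.7% |

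At a true difference of 10 points, false non-inferiority was 4.9% to 5.7% across both methods. A separate simulation of the logistic standardisation proposed here gave 4.0% to 5.1%, against 3.8% to 5.4% unadjusted.

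**5. What chance imbalance can do.** The SD of the between-arm difference in SLNB share is √(2π(1−π)/112), where π is the SLNB share. At π = 0.7 this is √(0.42/112) = 6.1 points; for π from 0.5 to 0.85 it is 6.7 to 4.8 points. With odds ratios of 2 and 1.5 at π = 0.7, the event rates are 6.2% without and 11.6% with SLNB. A 1.96-SD imbalance then moves the risk difference by 1.96 × 0.061 × 0.054 = 0.65 points. Over all scenarios the shift is 0.3 to 1.2 points, or about 0.3 to 1.3 patients in 112.

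For scale: with 11 events in the drain arm, 14 in the drain-free arm pass (difference 2.7 points, upper bound 9.6%) and 15 fail (3.6 points, upper bound 10.6%).

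**6. Per-protocol set.** The documents give no rate of departure from allocation, so this is an illustration only. Suppose the largest 5% to 10% of drain-free wounds, and none in the drain arm, left the per-protocol set, with an odds ratio of 1.5 to 2 per SD of wound surface. At a true 20% versus 10%, the unadjusted comparison would then declare non-inferiority in roughly 8% to 14% of trials instead of 5%. Re-running this case with standardisation for wound surface removed most of the excess but not all of it.

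**The case against.** The strongest reply is that nothing here is wrong. The article fixes a difference in proportions and a limit. It does not forbid covariates, and a full protocol or analysis plan may name them. Chance imbalance is already part of what a confidence interval covers. Every prognostic strength used above is assumed, and if the variables do not predict aspiration, nothing is gained. Excluding modified radical mastectomy already narrows axillary differences. Most of this stands, and it sets the size of the point.

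What remains is that the decision rule is stated without adjustment while two usable variables are collected, and that using them keeps the same scale and limit. The reply about chance imbalance also applies fully only to the intention-to-treat set. It is weaker for a per-protocol set formed after unblinded allocation.

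A reader might infer three stronger claims. The documents support none of them.

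- *The unadjusted test is biased or the trial underpowered for lack of covariates.* It held its error rate near 5%, and 112 per arm was reached without any covariate gain.
- *Allocation should have used these variables.* Wound surface is continuous, and its order relative to randomisation is not stated, so it cannot be assumed available then. For SLNB, even a 1.96-SD imbalance moves the result by at most about 1.2 points. Unstratified blocks are not a fault here.
- *The per-protocol result will favour drain-free surgery.* Step 6 shows what could happen under a deliberately adverse pattern. No passage says that it will.

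**Conclusion.** This is a worthwhile but minor improvement. The gain is about 0 to 2.5 points of power, given one-sided 5%, a 10% event rate, an SLNB share of 50% to 85% and the odds ratios assumed above. There is some added protection in the per-protocol analysis, of a size that the documents do not allow one to fix. Adjustment covers these two variables only. It does not repair selection on anything else, nor fully repair a region of wound sizes missing from one arm. The unstated confidence level matters far more: with a two-sided 95% interval, power at 112 per arm is 70.3%. That is a separate point.

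**What to change.** Keep the 10-point limit on the difference in proportions. Pre-specify that this difference is estimated by standardisation (g-computation) from a logistic model with arm, SLNB (yes/no) and wound surface. Apply it to both the per-protocol and the intention-to-treat analyses, and report the unadjusted difference as sensitivity analysis. State that wound surface is recorded before the allocation is opened, so that knowledge of the arm cannot influence it.

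Cost: a little more analysis work and no new data. With about 22 expected events the model should hold no covariates beyond these two. The order of measurement and allocation has to be fixed in theatre, which is a small change in conduct as well as in analysis.

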#### Secondary study parameter(s)

The proportion of patients with a surgical site infection will be compared between groups using Pearson’s chi-squared test. Differences in the mean scores on the SF-12 and the NRS for pain and for cosmesis will be compared using the independent-samples t-test. Poisson regression will be used to compare the number of outpatient department visits, measured during the first 6 months post-operatively. All secondary parameters will be tested on the intention to treat sample, and are measured over the first 6 months after treatment.

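### Per protocol alone can carry the non-inferiority claim: intention to treat is only a sensitivity analysis, and no rule covers disagreement between the two

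*Protocol article*

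**What the plan says.** Under Primary study parameter(s), the upper confidence bound for the difference in the proportion aspirated within 6 months is compared with the 10% margin: "In case the upper bound is below the non-inferiority limit, non-inferiority will be concluded". The next sentence names the analysis sets: "we will perform a per protocol analysis and an intention to treat analysis as sensitivity analysis". The natural reading is that per protocol decides and intention to treat supports. The section does not require the intention-to-treat bound to meet the margin as well, and it gives no rule for discordant results.

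Under Secondary study parameter(s) the choice is the other one: "All secondary parameters will be tested on the intention to treat sample". The primary claim is therefore the only one that rests on a set from which randomised patients can be removed.

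Two design features bear on this. The Blinding section says that "no blinding is possible due to the visibility of the drain". The Randomization section places allocation during the operation, half an hour before the wound is closed.

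**The concern.** A per-protocol comparison keeps the protection of randomisation only if those removed are, arm by arm, prognostically like those who stay. Here the surgeon learns the allocation while the wound is still open. A drain placed despite a no-drain allocation could plausibly go to a wound judged more likely to collect fluid, and that patient would then leave the drain-free per-protocol set. If this happened mainly in the drain-free arm, that arm's aspiration rate would be understated.

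Under the rule as written, a per-protocol pass is enough even when the comparison of all randomised patients misses the margin. What is at stake is the trial's one confirmatory claim, which the Discussion says could lead to drains being omitted.

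**Working it through.** **Inputs from the Sample size section.** Expected rate: "we estimate that about 10% of women in each group require seroma aspirations". Margin: 10 percentage points. Power: "To be able to have 80% power to reject the null-hypothesis that drain free mastectomy is inferior". Evaluable patients: "we need to include at least 112 patients per group". After allowing for 10% drop-out: 125 per group. No significance or confidence level is stated.

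**Step 1: reproduce the plan's figure.** n per group = (z₁₋α + z₀.₈₀)² × [p₁(1−p₁) + p₀(1−p₀)] / margin², with p₁ = p₀ = 0.10, so the bracket is 0.18.
- One-sided 0.05: (1.645 + 0.842)² × 0.18 / 0.01 = 111.3, so 112; 112 / 0.9 = 124.4, so 125. Both match the plan.
- One-sided 0.025: 141.3, so 142, and 158 after drop-out. This does not match.

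I therefore infer one-sided 0.05 (a two-sided 90% interval) and show 0.025 as the alternative.

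**Step 2: can exclusions reverse the verdict?** Upper limit = d + z × √[p₁(1−p₁)/n₁ + p₀(1−p₀)/n₀], drain-free minus drain. All counts are assumed.

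| Drain-free v drain | Difference (points) | Upper, z = 1.645 | Upper, z = 1.96 |
|---|---|---|---|
| Intention to treat, 17/125 v 12/125 | 4.0 | 10.65 fails | 11.92 fails |
| 7 drain-free excluded, 3 aspirated: 14/118 v 12/125 | 2.3 | 8.80 passes | 10.06 fails |
| 7 drain-free excluded, 2 aspirated: 15/118 v 12/125 | 3.1 | 9.76 passes | 11.04 fails |
| 7 drain-free excluded, 1 aspirated: 16/118 v 12/125 | 4.0 | 10.72 fails | 12.01 fails |
| 7 excluded in each arm, 3 aspirated in each: 14/118 v 9/118 | 4.2 | 10.57 fails | 11.79 fails |
| 3 drain-free excluded, all aspirated: 14/122 v 12/125 | 1.9 | 8.30 passes | 9.53 passes |

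For the second row: d = 0.1186 − 0.0960 = 0.0226; standard error = √(0.000886 + 0.000694) = 0.0398; 0.0226 + 1.645 × 0.0398 = 0.088.

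The verdict reverses when those excluded are at raised risk and come from the drain-free arm only. It does not reverse when they are at about average risk, or when the same loss occurs in both arms.

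**Step 3: false-claim rate at the margin.** True rates 20% v 10%, 125 per arm, exact binomial enumeration, one-sided 0.05, exclusions from the drain-free arm only:
- Intention to treat: 5.5%.
- 6 excluded with an assumed aspiration risk of 40% to 60%: 8.3% to 12.3%.
- 12 excluded with the same assumed risks: 12.9% to 26.2%.
- 6 or 12 excluded with the arm's own 20% risk: 5.4% to 5.5%, so no inflation.

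**Step 4: cost of requiring both sets.** True rates 10% in both arms, 125 per arm by intention to treat, 112 per arm per protocol, exclusions unrelated to outcome, exact enumeration.

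| One-sided level | Per protocol | Intention to treat | Both |
|---|---|---|---|
| 0.05 | 80.3% | 84.5% | 78.6% |
| 0.025 | 71.6% | 75.4% | 68.9% |

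**The case against.** The strongest reply is that per protocol as the primary set is a recognised choice for non-inferiority. Intention to treat can dilute a real difference: a drain-free patient who receives a drain stays in the drain-free arm and pulls the arms together. This stands. It is a reason to keep the per-protocol analysis, but not a reason to let it decide alone.

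A reader might infer that the likely deviations push the result towards non-inferiority, with no matching loss in the drain arm. The document does not support that. The section on mastectomy with low vacuum drainage requires removal by 48 hours whatever the output. A drain left longer because output was high would be a drain-arm deviation also linked to seroma risk, and excluding such patients would work against non-inferiority. The net direction is unknown, and so is the frequency of crossover, which randomisation late in the operation may keep low.

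A reader might also suppose that aspirations falling outside the three criteria for clinically significant seroma would be removed as deviations, taking the event with them. Nothing in the text says so. Membership of the per-protocol set may be defined in the full protocol or analysis plan, and its absence from the article is not counted here.

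Finally, intention to treat is prespecified and the article commits to full, CONSORT-based reporting, so a discordant result should be visible. What remains is that the stated rule would still call the trial non-inferior.

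**Conclusion.** The point holds as a gap in the decision rule. It is not evidence of an established bias, and choosing per protocol as primary is not itself an error. As written, non-inferiority can be concluded when the comparison of all randomised patients misses the 10-point margin.

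That outcome depends on exclusions that are related to prognosis and unequal between arms. Under that assumption a handful is enough: seven exclusions with two or three aspirated at the inferred 90% interval, or three exclusions, all aspirated, at either confidence level. The example of seven with three aspirated does not reverse at 95% (10.06 points), so the number needed depends on the unstated level, but the possibility of a reversal does not. The counts and risks are illustrations; the document gives no expected crossover rate.

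**What to change.** This is a cheap improvement. Keep the per-protocol analysis and replace the conclusion sentence under Primary study parameter(s) with wording such as: non-inferiority will be concluded only if the upper confidence limit for the difference is below 10 percentage points in both the per-protocol and the intention-to-treat analyses. This guards against informative exclusion on one side and dilution on the other, and it settles in advance what a discordant result means.

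The cost is one sentence and a small loss of power, from 80.3% for per protocol alone to about 79% for both, on the step 4 assumptions at the inferred one-sided 0.05. The planned 250 patients need not change for this reason.
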